### Safety assessments

The Juanbi pill has been used for hundreds of years in China, and the herbs in the Juanbi pill are safe according to the recommended amount in *Pharmacopoeia of the People’s Republic of China* (2015 version). Our preliminary experiment from December 2015 to May 2016 into the use of the Juanbi pill combined with MTX versus MTX alone did not show any side effects during the 3-month treatment period or in the 3-month follow-up period. We still need to perform a series of measures including subjective description and laboratory tests (especially on gastrointestinal intolerance, irritability, and kidney and liver damage) to assess the safety of the Juanbi pill during the entire trial.

At each visit, patients will be asked whether there are any adverse effects during the study period. In addition, we will perform laboratory testing of the participants’ blood, urine, feces, and kidney and liver function. We are ready to provide an appropriate treatment to the participant immediately if an adverse event is reported. Emergency services will be provided in the case of serious adverse events, and we will be prepared to report the event to the Institutional Review Board within 24 h from the time of recognition.

### Participant timeline

Study recruitment started in December 2016, and is expected to end in December 2017. The final follow up of all participants will end on 31 December 2018. The overview of the participant process is shown in Fig. 1, and the schedule of enrollment and assessments is provided in Fig. 2.

**Fig. 2 Fig2:**
[figure not shown]
Schedule of enrollment and assessments. ACR, American College of Rheumatology; DAS28, 28-joint Disease Activity Score; HAQ-DI, Health Assessment Questionnaire-Disability Index; AIS, Athens Insomnia Scale; SF-36, 36-item Short-Form Health Survey; MTX, methotrexate

### Sample size calculation

We calculated the sample size according to our primary study. We conducted a preliminary experiment from December 2015 to May 2016 into the efficacy of the Juanbi pill combined with MTX versus MTX alone, and we found that patients taking the Juanbi pill combined with MTX achieved 84.8% ACR50, whereas patients in the MTX group achieved 55.5% ACR50 response. According to the formula of the rate in completely random design:$$ \mathrm{n}1=\mathrm{n}2=\frac{\left[{u}_{\alpha /2}\sqrt{2\overline{p}\left(1-\overline{p}\right)}+{u}_{\beta}\sqrt{p_1\left(1-{p}_1\right)+{p}_2\left(1-{p}_2\right)}\right]\ }{{\left({p}_1-{p}_2\right)}^2}, $$

where n_1_ and n_2_ are the number of participants in the Juanbi and placebo groups, respectively, and *u*_*α*/2_=1.96 when type 1 error is 0.05, *u*_*β*_ = 1.282 when type II error is 0.1 in two-sided tests: $$ \overline{p} $$ is the mean of *p*_1_ and *p*_2_ [31]. It was estimated that approximately 50 participants per group were needed to achieve 90% power and a (two-sided) 5% significance level in detecting treatment differences. Thus, the final sample size has been set at a total of 120 patients (60 in each group), considering a 20% dropout rate. Forty participants (20 in the treatment group and 20 in the placebo group) from the three centers will be recruited.

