## Methods/design

### Study design

This study is a multicenter, randomized, double-blinded, placebo-controlled clinical trial with two parallel arms (Fig. 1). The aim of the study is to evaluate whether the Juanbi pill combined with MTX is effective for the management of active RA. In total, 120 patients with active RA will be recruited (60 patients per arm) from centers in Shanghai, China, from Longhua Hospital affiliated with Shanghai university of Traditional Chinese Medicine, Yueyang Integrated Medicine Hospital affiliated with Shanghai University of Traditional Chinese Medicine, and Shanghai Guanghua Hospital of Integrated Traditional Chinese and Western Medicine. The Standard Protocol Items: Recommendation for Interventional Trials (SPIRIT) 2013 checklist is shown in Additional file 1.

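### The sample-size paragraph needs three corrections: a recruitment figure of 40 that contradicts 120, a formula printed without its square, and a dropout allowance that leaves 48 per arm where 50 are required

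*Protocol article*

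**What the plan says.** The Study design section gives the target: "In total, 120 patients with active RA will be recruited (60 patients per arm"). The Abstract also gives 120 in total.

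The Sample size calculation section takes its response rates from a preliminary study: "patients taking the Juanbi pill combined with MTX achieved 84.8% ACR50", whereas "patients in the MTX group achieved 55.5% ACR50 response". It introduces its formula with the words "According to the formula of the rate in completely random design" and defines the normal deviates as "1.96 when type 1 error is 0.05" and "1.282 when type II error is 0.1 in two-sided tests". In the printed formula the denominator is squared and the bracketed numerator is not. The section reports a need for about 50 per group at 90% power and a two-sided 5% level, and concludes that "the final sample size has been set at a total of 120 patients (60 in each group), considering a 20% dropout rate". The next and last sentence reads: "Forty participants (20 in the treatment group and 20 in the placebo group) from the three centers will be recruited".

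**The concern.** Three things in this one paragraph do not fit together.

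1. **Recruitment total.** Read literally, the last sentence plans 40 patients across all centres. The sentence before it, the Study design section and the Abstract plan 120. The Quality control section has monthly supervision check that each centre has met its planned number, and the sentence about forty is the only one in the article that could supply a per-centre figure. It should therefore be unambiguous.
2. **Formula.** A reader who puts the stated inputs into the printed formula does not obtain the stated 50.
3. **Dropout.** Sixty per arm is presented as allowing for 20% dropout, but 20% loss from 60 leaves fewer than the 50 said to be needed. The claim of 90% power after 20% dropout is therefore slightly too favourable.

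At stake are a clear recruitment target, a calculation that can be reproduced, and a power statement that readers can rely on if the result is negative.

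**Working it through.** **Inputs**, all from the Sample size calculation section: p1 = 0.848, p2 = 0.555, u(α/2) = 1.96, u(β) = 1.282, 20% dropout. Derived: p̄ = (0.848 + 0.555)/2 = 0.7015; p1 − p2 = 0.293; 0.293² = 0.08585.

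**Step 1. The bracketed numerator**

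- 1.96 × √(2 × 0.7015 × 0.2985) = 1.96 × 0.6471 = 1.2684
- 1.282 × √(0.848 × 0.152 + 0.555 × 0.445) = 1.282 × 0.6131 = 0.7860
- Sum = 2.0544

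**Step 2. Reproducing the stated 50 per group**

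- With the numerator squared: 2.0544² / 0.08585 = 49.16, so 50. This matches the article.
- As printed, without the square: 2.0544 / 0.08585 = 23.93, so 24. This does not match.

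The stated 50 therefore comes from the squared form. The error lies in the printed formula, not in the number used.

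**Step 3. Dropout**

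- 50 × 1.2 = 60, which is the article's figure.
- 60 × (1 − 0.20) = 48, below 50 and also below the unrounded 49.16.
- To retain 50 after 20% loss: 50 / (1 − 0.20) = 62.5, so 63 per arm, or 126 in total.
- Dropout that 60 per arm can absorb while retaining 50: (60 − 50)/60 = 16.7%.

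**Step 4. Power**, solving the same squared formula for power: Φ[(0.293 × √n − 1.2684) / 0.6131]

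| n per arm | Power |
|---|---|
| 48 (60 less 20%) | 89.3% |
| 50 (stated requirement) | 90.5% |
| 60 (no loss) | 94.9% |
| 63 (no loss) | 95.8% |

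The shortfall after 20% dropout is 90 − 89.3 = 0.7 percentage points against the stated 90%.

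**Step 5. Forty against 120**

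- Three centres are named in the Study design section.
- 40 × 3 = 120 and 20 × 3 = 60 per arm, exactly the totals stated elsewhere.
- No sentence in the article says that the forty are per centre.

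**The case against.** The case for leaving the paragraph alone is that nothing of substance turns on it. The Abstract, the Study design section and the preceding sentence all say 120, the arithmetic of three centres explains the forty, and planned numbers are checked centre by centre. The missing square changed no figure and may be a typesetting loss. The dropout step costs less than one point of power against a requirement that the article itself calls approximate.

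Most of this stands, and it limits the weight of the point. It does not make the text correct: the forty still reads as a total, the printed formula still fails to give 50, and 48 is still fewer than 50.

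Two stronger readings are tempting, and neither is supported.

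- A reader might infer that the trial may recruit only 40 patients and so have about 53% power (52.7% at 20 per arm by the same formula). The article taken as a whole does not plan such a trial; every other statement of the total is 120.
- A reader might infer that intention-to-treat analysis pulls power down to about 74%. That figure comes from counting all of a 20% dropout as non-responders: 0.8 × 0.848 = 0.678 against 0.8 × 0.555 = 0.444, with 60 per arm. The Statistical analysis section instead specifies last observation carried forward, under which a patient who met ACR50 at the last visit before leaving stays a responder. The article states no non-responder rule.

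**Conclusion.** The paragraph contains three errors of text or arithmetic, all of modest weight.

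- **The forty** contradicts 120 as worded. A dropped word is the probable explanation, but this is an inference for the sponsor to confirm.
- **The printed formula** is wrong (24 per arm); the stated requirement of about 50 is right for the stated inputs (49.2).
- **The dropout allowance** is wrong by 3 per arm (60 against 63), which lowers power after 20% loss to about 89%.

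None of this shows a materially underpowered trial at 120 patients. That conclusion concerns ACR50 only, takes the preliminary response rates of 84.8% and 55.5% as given, and uses the article's own normal-approximation formula. The article names no test for proportions. Fisher's exact test would give lower absolute figures (87.2% at 50 per arm, 85.3% at 48), but the difference between 48 and 50 remains small, at 1.9 points.

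**What to change.** 1. Confirm the intended meaning of the last sentence. If it is per centre, state 40 participants at each of the three centres (20 per arm), 120 in total.
2. Put the square on the bracketed numerator of the formula.
3. Keep 120 and restate the power claim in one of two equivalent ways: about 89% power after 20% dropout, or 90% power with up to about 17% dropout.

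The cost is a few edited sentences and a slightly less favourable power statement. No patients are added, and the design and analysis do not change.

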### Statistical analysis

Efficacy and safety analyses will be conducted according to the intention-to-treat principle. The method of last observation carried forward will be applied in analysis of missing values. All statistical analyses will be performed using Statistical Packages of Social Sciences software (SPSS) (version 21.0). A *p* value < 0.05 will be defined as a statistically significant result. Means and standard deviations will be used to describe the continuous variables, such as demographic and clinical outcome variables, whereas percentages will be used for categorical variables such as the rate. Continuous variables following the normal distribution will be analyzed by Student’s *t* test; otherwise, non-parametric tests will be used to compare group differences.

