The duration of the intervention is 3 months, and follow up is 9 months. Study visits will take place at baseline and at 2, 4, 8, 12, 24, and 52 weeks. Every patient will be asked to visit within 3 days of the given time point.

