### Randomization and allocation

Randomization will be conducted by a credible pharmaceutical manufacturer (Jiangyin Tianjiang Pharmaceutical Co., Ltd), which will provide both the Juanbi pill and the placebo. A random number list will be generated using Excel (Office 2016, Microsoft Corporation) to randomize participants either to the Juanbi pill group or the placebo group in a 1:1 ratio. When a participant is recruited, the investigator will provide the pharmaceutical manufacturer with a number, and the pharmaceutical manufacturer will randomly post the Juanbi pill or the placebo to the participant according to the random number list. The number provided and the corresponding number list will be recorded and will be kept in a locked cabinet at the pharmaceutical company.

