### Data collection and monitoring

This is a 12-month clinical trial in which participants are required to take the research medication for 3 months with follow-up visits at 6 and 12 months, attending seven assessment visits in all. Participants will receive disease activity assessment seven times (at baseline and 2 weeks, and at 1, 2, 3, 6, and 12 months), and six safety assessments (at baseline, and at 1, 2, 3, 6, and 12 months). Longhua Hospital affiliated with Shanghai University of Traditional Chinese Medicine is responsible for quality control.

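### Safety is placed under intention to treat, with last observation carried forward and no safety exemption: adverse-event rates may be diluted and laboratory comparisons biased in either direction

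*Protocol article*

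**What the plan says.** Two consecutive sentences in the Statistical analysis section set the rule. The analysis principle is "Efficacy and safety analyses will be conducted according to the intention-to-treat principle". The missing-data rule is "The method of last observation carried forward will be applied in analysis of missing values". The second sentence is general: it does not name laboratory or adverse-event data, and it does not exclude them. The section describes no separate safety set.

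Four other places matter:

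- **Randomization and allocation:** product reaches the patient after recruitment, because "the pharmaceutical manufacturer will randomly post the Juanbi pill or the placebo to the participant according to the random number list".
- **Safety assessments:** the plan is that "we will perform laboratory testing of the participants’ blood, urine, feces, and kidney and liver function", and kidney and liver damage are singled out for attention.
- **Data collection and monitoring:** the schedule has "six safety assessments (at baseline, and at 1, 2, 3, 6, and 12 months".
- **Interventions:** "The duration of the intervention is 3 months, and follow up is 9 months".

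The exclusion criteria remove patients whose liver and kidney function is abnormal at entry.

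**The concern.** Intention to treat preserves the randomised comparison for efficacy. Applied to safety, it counts people who were never exposed to the product among those at risk of its side effects. Delivery by post after randomisation makes non-dosing possible. Carrying the last value forward raises a second problem: it replaces laboratory results that were never measured after dropout with an earlier result, which for an early leaver is the pre-dose one.

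The Background gives estimating safety as one purpose of the trial, and the Discussion expects the results to inform clinical decisions and possibly guidelines. The Safety assessments section reports that the preliminary experiment showed no side effects, so adverse-event counts may well be low. The absolute rates and the laboratory summaries will then carry most of the safety message.

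**Working it through.** **The plan's own figures.** The article states no safety rate, no number never dosed and no size for a safety set. Its only computed figure is the ACR50 sample size. With 84.8% versus 55.5%, two-sided 5% and 90% power, the pooled formula with its numerator squared gives 49.2, rounded up to 50 per group, which agrees with the article. Only the resulting 60 per arm ("the final sample size has been set at a total of 120 patients (60 in each group") is used below. Event rates, never-dosed shares and laboratory patterns are assumptions.

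**1. Undosed patients in the denominator.** Let p be the event rate in dosed patients, u the never-dosed share and q the event rate in the undosed. The intention-to-treat rate is p(1 − u) + qu. With q = 0 and equal u in both arms, the risk difference is (p₁ − p₀)(1 − u) and the risk ratio stays p₁/p₀. Assume 30% versus 10%. The last two columns compare power on all 60 per arm at the diluted rates with power on the 60(1 − u) dosed patients at the true rates.

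| u | Rates by intention to treat | Risk difference (points) | Risk ratio | Power, intention to treat | Power, dosed only |
|---|---|---|---|---|---|
| 0% | 30.0% vs 10.0% | 20.0 | 3.0 | 0.789 | 0.789 |
| 2% | 29.4% vs 9.8% | 19.6 | 3.0 | 0.779 | 0.781 |
| 5% | 28.5% vs 9.5% | 19.0 | 3.0 | 0.762 | 0.768 |
| 10% | 27.0% vs 9.0% | 18.0 | 3.0 | 0.734 | 0.745 |

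The relative fall in rates and risk difference equals u, that is 2% to 10%. Compared with analysing dosed patients only, power falls by 0.2 to 1.1 percentage points.

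The case q = 0 is the least favourable of those considered, because undosed patients may still take MTX and report events. With p = 20% and q = 10% (assumed), u = 5% gives 0.20 × 0.95 + 0.10 × 0.05 = 19.5%, against 19.0% with q = 0. At u = 10% the figures are 19.0% and 18.0%.

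**2. Carry-forward that hides toxicity.** By the schedule in Data collection and monitoring, the first safety assessment after baseline is at month 1. A patient who leaves before then keeps the eligibility-screened baseline liver and kidney result at all five later assessments. If 10% of an arm leaves this early and the true abnormality rate is 20% in leavers and stayers alike (both assumed), the reported rate is 0.20 × (1 − 0.10) = 18%.

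More generally, suppose a laboratory difference grows linearly over treatment and a share d of the active arm leaves at fraction f of exposure. Carry-forward then keeps 1 − d(1 − f) of the difference:

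- d = 10%: 93% at f = 1/3 and 97% at f = 2/3.
- d = 20%: 87% at f = 1/3 and 93% at f = 2/3.

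**3. Carry-forward that creates a difference.** Suppose an on-treatment rise of 10 units in the active arm has resolved by month 12, so the true difference there is 0. If 10% to 20% of that arm left with the raised value as their last, the carried-forward month-12 difference is 10 × 0.10 = 1 unit to 10 × 0.20 = 2 units. This bias is away from no difference.

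**The case against.** The case for leaving the plan alone has real weight.

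- **Direction.** A reader might infer that the plan as a whole biases safety towards no difference. The documents do not support that. With 3 months on treatment and 9 months off, carrying a reversible abnormality forward pushes the other way (step 3), so the direction for laboratory values is not fixed.
- **Size.** A reader might take the planning phrase "considering a 20% dropout rate" as the share never dosed and shrink each arm's exposed group by a fifth. That is total dropout. Patients who start and later leave have been dosed and would remain in an at-least-one-dose set. No never-dosed number is given, and the monthly site supervision and monthly calls under Quality control make substantial undetected non-dosing less likely.
- **Comparison between arms.** If undosed shares are equal and the undosed have no events, the risk ratio is untouched and the loss of power is slight. If the undosed do have events on MTX, rates are diluted less.
- **Reach of the imputation rule.** Its use for laboratory values is inferred from a general sentence, and details of laboratory summaries often sit in an analysis plan that is not shown. In addition, the Safety assessments section could be read as putting laboratory tests at every visit, including week 2, which would narrow the early-leaver window.
- **Aim.** The stated purpose is to estimate safety. There is no safety hypothesis or margin.

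All of this limits the size of the problem. It does not remove it. The article names safety and assigns it the efficacy principle, so this is a stated rule and not a gap left to another document. The carry-forward sentence follows directly with no exemption. Bias of uncertain direction is itself a reason not to carry safety values forward.

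**Conclusion.** The point holds as a minor one that is cheap to correct. As written, the plan keeps never-dosed patients in the safety denominator, which tends to lower absolute adverse-event rates and risk differences: by a relative 2% to 10% if 2% to 10% are undosed and have no events, by less if they do have events, and not at all if everyone is dosed.

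Read literally, the carry-forward rule can bias liver and kidney comparisons either way. It understates toxicity in patients who leave early with normal baseline values, and it creates or prolongs a difference when a reversible on-treatment abnormality is carried into the off-treatment period. These conclusions rest on assumed event rates, undosed shares and laboratory patterns, and on the carry-forward sentence covering safety data.

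**What to change.** In the Statistical analysis section:

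- limit intention to treat, and any imputation, to efficacy;
- analyse safety in participants who took at least one dose of study product, grouped by product received;
- summarise laboratory values as observed at each assessment, without carry-forward.

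This is a change of wording plus one extra analysis set. It needs no new visits, data or patients. The downside is a slightly smaller safety denominator if some patients turn out never to have been dosed. Reporting adverse events against exposure time would be a reasonable option, but it is not needed to settle this point.

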The van der Heijde modified Sharp score is the radiographic assessment of the *erosion* and *the joint narrowing* in the 10 metacarpophalangeal joints, 8 proximal interphalangeal joints, 10 metatarsophalangeal joints, and 2 interphalangeal joints of the big toes. In addition, erosion is also assessed in the two interphalangeal joints of the thumbs, first metacarpal bone, radius, ulnar bones, trapezium and trapezoid, navicular bones, and right and left lunate bones bilaterally, whereas joint narrowing is also assessed in the third, fourth, and fifth carpometacarpal joints, multiangular-navicular joints, capitate-navicular-lunate joints, and right and left radiocarpal joints bilaterally. The maximum erosion score in the hand is 5, and in the foot it is 10, according to the degree of erosion. Thus, the maximum number of erosions in the hand is 160, and in the feet it is 120. The grade of joint space narrowing is as follows:1 = focal or doubtful2 = general, less than 50% of the original joint space3 = general, more than 50% of the original joint space or subluxation4 = no joint space remaining, luxation, or ankylosis

Therefore, the maximum score for joint space narrowing is 120 in the hand and 48 in the feet. The van der Heijde modified Sharp score is the sum of the erosion and joint space narrowing score [16, 25].

The ACR50 and DAS28 will be estimated at baseline and after 1, 2, and 3 months of treatment, and at the 6-month and 12-month follow up. The van der Heijde modified Sharp score will be measured only at baseline and after 12 months.

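### Continuous outcomes, including the primary DAS28 and modified Sharp changes, are to be compared by a t test or unnamed non-parametric tests chosen by distribution, with baseline subtracted but not used as a covariate

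*Protocol article*

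**What the plan says.** The Statistical analysis section gives one rule for all continuous outcomes: "Continuous variables following the normal distribution will be analyzed by" Student's t test, and "otherwise, non-parametric tests will be used to compare group differences". It names no covariate and no model, does not say which non-parametric tests are meant, and does not say how normality will be judged. Its threshold is that a p "value < 0.05 will be defined as a statistically significant result".

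Under Primary outcome measure, DAS28 is a change from before treatment to 1, 2 and 3 months, and the modified Sharp score is a between-group difference in the change over 12 months. Baseline values are collected for both: "The ACR50 and DAS28 will be estimated at baseline and after 1, 2, and 3 months of treatment", with further assessments at 6 and 12 months, and the Sharp score is read at baseline and 12 months only. The Abstract lists DAS28 as primary at 3 months and the other visits as secondary. On either listing the same scale is tested at several visits under the same rule. HAQ-DI, pain, patient global assessment, AIS and SF-36 are also analysed as changes from baseline.

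**The concern.** The rule is a stated choice of method, not a detail left for later, and it has two weaknesses.

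- **Precision.** A t test on change fixes the coefficient of baseline at 1. When the true regression slope of follow-up on baseline is not 1, this leaves avoidable noise in the estimate. It also over- or under-corrects a chance imbalance at baseline. Only ACR50 was used to size the trial, so nothing in the article shows how much power DAS28 or the Sharp score has to spare.
- **Effect measure.** The test depends on how each variable looks. DAS28 could be compared by a t test at month 1 and by a rank-type test at month 3. The first estimates a mean difference in DAS28 units. The second, as usually reported, gives a p value and no effect on that scale. Results across visits would then have no common measure.

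**Working it through.** **What the plan's own figure covers.** The inputs, from Sample size calculation, are 84.8% and 55.5% ACR50, two-sided 5% and 90% power. The mean rate is (0.848 + 0.555)/2 = 0.7015. With the numerator squared, as the standard two-proportion formula has it:

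- 1.96 × √(2 × 0.7015 × 0.2985) = 1.268
- 1.282 × √(0.848 × 0.152 + 0.555 × 0.445) = 0.786
- (1.268 + 0.786)² / 0.293² = 49.16, rounded up to 50 per group

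The stated figure of about 50 reproduces. It concerns ACR50 only, so no target for DAS28 or the Sharp score is available to check against.

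**Change score against ANCOVA.** The Statistical analysis section does not itself say that the test is applied to the change; I take that from the outcome definitions. Let r be the baseline-to-follow-up correlation and k the follow-up SD divided by the baseline SD. In units of the baseline variance:

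- variance of the change score: 1 + k² − 2rk
- residual variance under ANCOVA: k²(1 − r²)
- the difference between the two: (1 − rk)², which is never negative

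So in large samples ANCOVA is never less precise, whatever r and k are. Estimating the slope costs about 1/(120 − 4) = 0.9% in variance at 120 patients.

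The article gives neither r nor k, so all values below are assumptions.

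*Equal SDs (k = 1).* The ratio reduces to (1 − r²)/(2(1 − r)) = (1 + r)/2.

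| r | ANCOVA variance / change-score variance | patients needed by the t test, relative to ANCOVA |
|---|---|---|
| 0.3 | 0.65 | 1/0.65 = 1.54 |
| 0.5 | 0.75 | 1/0.75 = 1.33 |
| 0.6 | 0.80 | 1/0.80 = 1.25 |
| 0.9 | 0.95 | 1/0.95 = 1.05 |

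In power terms, where ANCOVA would have 90%, the change-score t test has Φ(3.2416 × √((1 + r)/2) − 1.96). That is 74% at r = 0.3, 80% at r = 0.5 and 85% at r = 0.7.

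*Larger spread at follow-up (k = 1.3).* This is plausible for DAS28, because entry requires a DAS28 above 3.2, which can narrow the baseline distribution.

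- r = 0.3: 1.69 × 0.91 / (2.69 − 0.78) = 1.538/1.91, about 0.81
- r = 0.5: 1.69 × 0.75 / (2.69 − 1.30) = 1.268/1.39 = 0.91
- r = 0.6: 1.69 × 0.64 / (2.69 − 1.56) = 1.082/1.13 = 0.96

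The gain is then about 4 to 19% of the variance, where equal SDs gave 20 to 35%. If follow-up values were instead less spread than baseline, the gain would exceed the equal-SD figures.

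**Data-dependent test.** No arithmetic applies here. The rule works variable by variable, and DAS28 change is a separate variable at each visit. Nothing in the text ties the visits to one method.

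**The case against.** The strongest reply is that a two-sample t test on change is unbiased and valid under randomisation, so this is a preference for efficiency and not the correction of an error. That stands as far as validity goes, and no inflation of the type I error is claimed. It does not defend the choice, because the baseline values are collected anyway and adjustment costs almost nothing.

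It can also be said that the gain is easily overstated. This stands too. The simple ratio (1 + r)/2 needs equal SDs, and the gain is small for an outcome that tracks its baseline closely, as the Sharp score may. The ranges above allow for both.

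On the choice of test, the section does promise means and SDs for clinical outcomes, so a reader would not be left with a p value alone. But descriptive means are not a between-group estimate with an interval from the analysis that supplies the p value.

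Three stronger readings may tempt a reader, and the article does not support them:

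- *Baseline is ignored.* It is not. DAS28 and Sharp are changes and ACR50 is improvement from baseline. Baseline is subtracted but not used as a covariate.
- *No comparison of ACR50 is planned.* The analysis text says only that "percentages will be used for categorical variables such as the rate". But the sample size rests on a comparison of two rates, since "patients taking the Juanbi pill combined with MTX achieved 84.8% ACR50" "whereas patients in the MTX group achieved 55.5% ACR50 response". The name of the test is a detail that a condensed article may leave to the full protocol or SAP.
- *Centre is wrongly left out.* The design is described thus: "This study is a multicenter, randomized, double-blinded, placebo-controlled clinical trial with two parallel arms". The randomisation section describes no stratification by centre. The sentence on forty participants, 20 per group, agrees with 120 only if read as per centre, which is an inference. No between-centre variance is given, so no loss can be computed. A centre term may be left to the full protocol or SAP.

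**Conclusion.** The point holds as a recommended improvement to a stated method. The tests chosen for the continuous outcomes are valid but less precise than they need be, and the effect measure is left to the shape of the data and may change between visits.

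The direction of the precision loss does not depend on assumptions in large samples, but its size does. It is 20 to 35% of the variance for r of 0.3 to 0.6 with equal SDs, about 4 to 19% for the same r if the follow-up SD is 1.3 times the baseline SD, and about 5% at r = 0.9 with equal SDs. No shortfall against a stated power target is shown, because the article states none for DAS28 or the Sharp score. The lack of a common effect measure follows from the wording alone.

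**What to change.** In the Statistical analysis section, replace the distribution-dependent rule for continuous outcomes as follows.

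- **DAS28 and the other continuous outcomes:** ANCOVA, or a repeated-measures model over the visits, with treatment and baseline value. Report the adjusted mean difference and 95% CI at every visit, whatever the distribution looks like.
- **Modified Sharp change,** which is likely to be skewed: the baseline-adjusted mean difference with a bootstrap CI, and a rank test as a supporting analysis only.

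The change should be fixed in writing before unblinding. It needs no new data, visits or patients, and standard software can run it. A centre term and a named comparison for ACR50 could be added in the same edit as optional clarifications; they are not part of this point.
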